---

## LIST OF ABBREVIATIONS

|              |                                                |
|--------------|------------------------------------------------|
| ACTG  | AIDS Clinical Trial Group                      |
| AIDS  | Acquired Immune Deficiency Syndrome            |
| ART   | combination Anti-Retroviral Treatment          |
| CD4   | CD4-positive T-lymphocyte count                |
| DBS   | Dried Blood Spot                               |
| DLM   | Drug level monitoring                          |
| EDTA  | Ethylenediaminetetraacetic Acid                |
| EFV   | Efavirenz                                      |
| GCP   | Good Clinical Practice                         |
| HCT   | HIV Counseling and Testing                     |
| HIV   | Human Immunodeficiency Virus                   |
| IC    | Informed Consent                               |
| ICER  | Incremental Cost-Effectiveness Ratio           |
| LMIC  | Lower and Middle Income Countries              |
| NCG   | Ndlovu Care Group                              |
| NMC   | Ndlovu Medical Center                          |
| NRTI  | Nucleos(t)ide Reverse Transcriptase Inhibitor  |
| NNRTI | Non-Nucleoside Reverse Transcriptase Inhibitor |
| NVP   | Nevirapine                                     |
| PBMC  | Peripheral Blood Mononuclear Cells             |
| PI    | Protease Inhibitor                             |
| QoL   | Quality of Life                                |
| QALY  | Quality-Adjusted Life Year                     |
| RCT   | Randomized Clinical Trial                      |
| RLS   | Resource-Limited Settings                      |
| TLC   | Thin Layer Chromatography                      |
| UMCU  | University Medical Center Utrecht              |
| VL    | Viral Load                                     |
| WHO   | World Health Organization                      |

## 1 SUMMARY

|                         |                                                                                                                                                                                                                                                                                                                                                                                                                                                                                                                                                                                                                                                                                                                                                                     |
|-------------------------|---------------------------------------------------------------------------------------------------------------------------------------------------------------------------------------------------------------------------------------------------------------------------------------------------------------------------------------------------------------------------------------------------------------------------------------------------------------------------------------------------------------------------------------------------------------------------------------------------------------------------------------------------------------------------------------------------------------------------------------------------------------------|
| Rationale        | We propose a novel low-cost intensified HIV-1 treatment monitoring strategy that will allow for (1) detection of therapy failure at an early stage, (2) immediate identification of patients with major non-adherence to therapy enabling intensified and tailored adherence counselling, (3) early detection of drug resistance prior to accumulation of resistance mutations, and (4) avoiding treatment switches to second-line regimens when drug resistance is absent. As this strategy is expected to reduce the duration of viremia during therapy failure it is expected to contribute to lower rates of transmission of (drug-resistant) HIV.                                                                                                              |
| Objective        | We aim to perform a randomized clinical trial comparing the proposed intensified monitoring strategy with standard of care HIV-1 treatment monitoring in patients who have recently initiated ART. We aim to investigate the benefits and cost-effectiveness of the proposed strategy relative to the standard of care. We will assess the effect on (1) relative risk of development and accumulation of resistance, (2) prevention of unnecessary switches to second-line therapy and (3) resuppression rates after detected viral rebound. We also aim to estimate the effect of the proposed strategy on the transmission of (drug resistant) HIV, and to use trial data to study potential risk factors and determinants of non-adherence and therapy failure. |
| Study design     | An open-label randomised controlled trial.                                                                                                                                                                                                                                                                                                                                                                                                                                                                                                                                                                                                                                                                                                                          |
| Study population | HIV-positive men and women, 18 years and older, attending Ndlovu Medical Centre (Elandsdoorn, Limpopo, South Africa) and eligible to initiate or already receiving ART.                                                                                                                                                                                                                                                                                                                                                                                                                                                                                                                                                                                             |

## **Inclusion, exclusion and randomisation criteria**

### **Inclusion criteria**

- HIV-1 infected male or female patients
- For ART Naïve patients: Eligible for and intending to initiate ART at the clinical site
- For patients on ART: On ART  $\geq 1$  year. Last VL <6 months ago and <1000 copies/mL
- $\geq 18$  years of age
- Able to understand and willing to give informed consent

### **Exclusion criteria**

- Any serious unstable medical condition at study baseline
- Any criteria that in the opinion of the investigator indicate that the patient is unable to participate in the full study.

### **Randomisation criteria**

- Completion of six months of continuous ART
- For ART Naïve patients: A VL of <1000 copies/mL at the first VL measurement after initiation at month 6 of ART or a VL of >1000 copies/mL at month 6 of ART followed by a VL of <1000 copies/mL before or at month 9 of ART.
- No signs of active severe opportunistic infection requiring therapy at time point of randomization, excluding infection with *M. tuberculosis*.

## **Study outcomes**

### **Virological effects of intensified monitoring**

- Amount of drug resistance mutations per patient with therapy failure in each arm
- Selection of specific resistance mutations associated with multi-drug resistance in each arm
- Consequential loss of therapeutic options between arms
- Rate of virological failure in the absence of drug resistance between arms
- Rate of resuppression after detectable viremia in each arm
- Unnecessary treatment switches averted in the intervention arm and unnecessary therapy switches made in the control arm

- Loss of therapeutic options over time in the presence of a failing regimen in both arms
- The influence of genotypic resistance testing on the choice for a second line regimen in the intervention arm
- Time on a failing regimen per patient with therapy failure in each arm

#### Clinical effects of intensified monitoring

- Decrease in CD4 count during failure in each arm
- Quality of life in each arm
- Any event of patient morbidity and mortality that can be related to immunological failure in each arm

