### 3.2 Secondary objectives

#### 3.2.1 Clinical effects of intensified monitoring

To assess the impact of the intensified monitoring strategy on (1) Quality of Life (QoL), (2) patient morbidity and mortality and (3) rates of immunological recovery. Clinical effects will be studied as a secondary objective as it is unknown if the follow-up duration will allow expected differences between arms to become apparent.

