#### 5.1.2 Control arm follow-up – standard of care HIV treatment monitoring

300 patients randomly assigned to this arm will be monitored in full concordance with current South African NDoH guidelines in use at the study site. Viral load measurements will be performed at month 12 and 24 after start of ART (for newly initiated patients) or at month 12 and 24 after the last VL measurement (patients already on ART). If a VL >1000 copies/ml is detected, the patient is called back for counselling for therapy adherence and repeat VL measurement, 2 months after the initial VL measurement. If the repeat VL measurement is >1000 copies/ml after adherence counselling, this is taken to be indicative of therapy failure due to development of drug resistance and a switch to second line therapy is made, together with intensified adherence counselling, without verifying the cause of virological failure by

performing DLM or drug resistance testing. If VL drops to <1000 copies/ml after adherence counselling, the first line treatment is maintained. For a full overview of study visits and clinical algorithms in the control arm, see Figure 1: ITREMA study flowchart.

Sample collection in the control arm consists of storage of EDTA-derived plasma and a DBS at study baseline and at the subsequent study visits at month 3, 6, 9, 12, 15, 18, 21 and 24 of ART, as well as during any additional study follow-up visits in case of a VL >1000 copies/ml. Blood draws at baseline, month 3, 6, 12 and 24 after start of ART, and in case of follow-up after a VL >1000 copies/ml coincide with blood draws performed as part of standard of care. The following measurements will be performed on stored samples:

- An additional CD4 measurement at study month 6, in order to assess eligibility for randomisation and rate of CD4-count recovery.
- Retrospective VL testing on stored EDTA-derived plasma in case of clinical therapy failure, in order to retrospectively examine the duration of viremia.
- Retrospective drug resistance testing on stored DBS in case of clinical therapy failure to examine the accumulation of resistance mutations over time.
- Screening for transmitted drug resistance by drug resistance testing on stored DBS obtained as at baseline, prior to start of ART.

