| CD4                                                                                                                                                                                                                                                                                                                                                                                                                                                                                                                                                            |          |         | X       |             |             |         | X        |          |          |          | X        |                                  |                  |                                       |                       |                       |               |
| DBS and plasma storage (1 EDTA 9ml)                                                                                                                                                                                                                                                                                                                                                                                                                                                                                                                            | X        | X       | X       |             |             | X       | X        | X        | X        | X        | X        | X                                | X                | X                                     | X                     | X                     | X             |
| PBMC isolation (2 EDTA 9ml)                                                                                                                                                                                                                                                                                                                                                                                                                                                                                                                                    | X        |         |         |             |             |         |          |          |          |          |          |                                  |                  |                                       |                       |                       |               |

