## 6 OUTCOMES AND ANALYSIS OF RESULTS

### 6.1 Virological and clinical effects of intensified monitoring

Virological outcomes will be differences between arms in (1) the number of drug resistance mutations present, (2) the selection of specific resistance mutations associated with multi-drug resistance (presence of the K65R mutation, or the presence of >1 NNRTI mutation) and (3) consequential loss of therapeutic options. Furthermore, (4) the rate of virological failure in the absence of drug resistance in both arms, unnecessary treatment switches averted in the intervention arm and unnecessary therapy switches made in the control arm will be assessed. An averted case of unnecessary switching will be defined as two sequential elevated VL results in the intervention arm without presence of resistance mutations. Assessment of unnecessary switching in the control arm can be ascertained by retrospective genotypic resistance testing.

Additional virological outcomes will be (5) the time on a failing regimen, defined as the time during which viremia > 1000 copies/mL is maintained after the first instance of a viral load >1000 copies/ml (6) The loss of second line therapeutic options over time in the presence of a failing regimen. Comparison of the extent of drug resistance between both groups will allow for assessment of the clinical consequences of resistance development in both arms. (7) The influence of genotypic resistance testing on the choice for a second line regimen. Genotypic resistance testing results enable the physician to make an informed decision with regard to a follow-up regimen to the first-line regimen. By comparing the chosen regimens in the intervention and control groups, the effect of the availability of genotypic resistance data on clinical decision-making will be compared. These outcomes can be compared between both arms as VL and CD4 measurements will be performed retrospectively in the control group, resulting in an equal frequency of measurements between both arms.

Clinical outcomes will be decrease in CD4 count during failure, QoL as measured using a validated QoL questionnaire, and recorded events of patient morbidity and mortality that can be related to immunological failure.

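### Section 6.1 bases the CD4 comparison during failure on retrospective control-arm counts that the sampling plan does not provide; compare the scheduled CD4 counts in all randomised patients instead

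*Protocol*

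**What the plan says.** The Summary names "Decrease in CD4 count during failure in each arm" as an outcome, and section 6.1 repeats it: "Clinical outcomes will be decrease in CD4 count during failure". The objective in section 3.2.1 is wider. It asks about "rates of immunological recovery" and is not restricted to patients who fail.

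Section 6.1 justifies comparing outcomes between arms by stating that "VL and CD4 measurements will be performed retrospectively in the control group, resulting in an equal frequency of measurements between both arms".

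The sampling plan is in section 5.1.2 and Table 4. Section 5.1.2 states: "Sample collection in the control arm consists of storage of EDTA-derived plasma and a DBS at study baseline and at the subsequent study visits". After control-arm failure it lists two retrospective tests, VL on plasma and resistance on dried blood spots (DBS). The only CD4 in that list is at month 6, the point of randomisation. Table 4 has a row for "DBS and plasma storage (1 EDTA 9ml") at every study and call-back visit. Its CD4 row is filled at months 6, 12 and 24 only, for both arms. Section 5.2.8 stores PBMCs from all patients at baseline only; three-monthly PBMCs are for a subgroup and await an amendment.

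**The concern.** Section 6.1 makes comparability depend on measurements that nothing else in the protocol supplies. A later analysis plan cannot repair this, because it cannot create samples that were not taken. If the sentence is followed literally, the analyst will look for three-monthly control-arm CD4 counts and find counts at months 6, 12 and 24.

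Two further problems affect any CD4 comparison confined to failing patients. First, the interval between detection, action and the nearest CD4 depends partly on the arm. Second, being found to fail happens after randomisation and depends on how often VL is tested, which is part of the intervention. The failing groups are therefore not randomised groups, and a difference between them need not be an effect of monitoring. What is at stake is one secondary clinical outcome; no primary outcome or sample size depends on it.

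**Working it through.** **1. Is there a retrospective CD4?** The protocol gives no CD4 sample size or target to reproduce, so the check sets its sections side by side.

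| Element | VL | CD4 |
|---|---|---|
| Claimed retrospectively in controls (6.1) | yes | yes |
| Listed as a test after control failure (5.1.2) | yes, on plasma | no |
| Suitable material stored at all follow-up visits | plasma | none (plasma and DBS only) |
| In Table 4 at months 9, 15, 18, 21 | intervention arm | neither arm |
| In Table 4 at viremia call-backs | yes, at the first | no |

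That plasma and DBS hold no intact cells to count is general laboratory knowledge, not a statement in the protocol. Even without it, CD4 is absent from the list of tests and from the schedule. The 4 ml EDTA tube in Table 4 follows the CD4 row exactly: one at months 6, 12 and 24, zero elsewhere, including every call-back column.

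**2. CD4 timing against scheduled detection.** From a first VL above 1000 to the switch decision takes about two months in either arm (5.1.2, 5.1.3).

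| Detected at month | Arms | Interval to decision | Scheduled CD4 within it |
|---|---|---|---|
| 9 | intervention | 9–11 | none |
| 12 | both | 12–14 | month 12 |
| 15 | intervention | 15–17 | none |
| 18 | intervention | 18–20 | none |
| 21 | intervention | 21–23 | none |
| 24 | both | 24–26 | month 24 |

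Control detection at a scheduled VL always coincides with a CD4. Four of the six intervention VL visits (9, 15, 18, 21) have none. No such interval contains two counts. After detection at month 12 and a switch at month 14, the next CD4 is at month 24, 10 months later. After detection at month 24 there is no later CD4.

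**3. Number of failing patients.** Inputs: 300 per arm (5.1.2, 5.1.3); 20% failure and 10% loss per year, hence 15% over 18 months (6.7.3). These inputs reproduce two of the plan's figures: 14/0.20/0.85 = 82.4, stated as 83, and 10/0.20/0.85 = 58.8, stated as 59.

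- Retained: 300 × 0.85 = 255 per arm.
- Failing: 255 × 0.20 = 51 per arm, if the rate is equal in both arms.

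**4. Detectable difference.** δ = (1.960 + 1.282) × SD × √(2/n), two-sided 0.05, power 0.90. The protocol gives no CD4 SD, so a range is assumed, the same in both populations.

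| SD of change (cells/mm³, assumed) | 51 per arm | 255 per arm |
|---|---|---|
| 100 | 64 | 29 |
| 150 | 96 | 43 |
| 200 | 128 | 57 |

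If the effect exists only in the 20% who fail, the all-patient difference is one fifth of it. At SD 100, an all-patient difference of 28.7 then corresponds to 28.7/0.20 = 144 in failing patients, against 64 when they are compared directly.

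**5. Gain from adjustment.** A decrease is a change score, and section 6.7.2 plans unadjusted tests. With equal variances s² and correlation ρ, the change score has variance 2(1−ρ)s² and the adjusted analysis (1−ρ²)s². The ratio is (1+ρ)/2: 0.75 at ρ = 0.5 and 0.85 at ρ = 0.7, a saving of 25% and 15% (ρ assumed).

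**The case against.** The strongest reply is that the outcome is not unmeasurable. Section 6.1 defines time on a failing regimen by maintained viremia, not by the two months from detection to switch, and retrospective VL on stored plasma dates its onset in controls. A control whose viremia begins at month 15 and is found at month 24 has a CD4 before failure (month 12) and one during it (month 24). This stands: a coarse change over months 6–12 or 12–24 can be computed. It mixes time before failure, during failure and, in some patients, after action, and it does not supply the equal-frequency CD4 that section 6.1 claims.

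A reader might also infer that the arms are read at opposite phases, controls before action and intervention patients after it. The protocol does not support that as a general statement. Intervention failures found at months 12 or 24 match controls. A patient found at month 9 with no detectable drug level is not switched before the month-12 visit (5.2.4.1), when CD4 is drawn. The mismatch is partial.

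It can be said, too, that the recovery data are collected: section 5.1.2 takes the month-6 CD4 partly to assess recovery. That is right. What is missing is an outcome that uses those data as section 3.2.1 asks.

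Finally, details of covariate adjustment may be left to an analysis plan. The contradiction in section 6.1 and the choice of population may not, because the protocol itself fixes both.

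**Conclusion.** The point holds as a contradiction within the protocol plus a poorly chosen comparison. The retrospective control-arm CD4 that section 6.1 relies on has no stored material suited to it, no listed test and no scheduled visit. What remains in failing patients is a coarse change with partly arm-dependent timing, in a subset of about 51 per arm defined after randomisation.

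Two stronger readings should be avoided. One is that moving from 51 to 255 patients per arm is a gain in power. The detectable difference does fall by a factor of about 2.2, but an effect confined to failing patients is diluted fivefold, so the all-patient analysis could be less sensitive. The other is that adjustment saves 25–49% of the variance. That is 1−ρ² set against an unadjusted month-24 value, which is not the planned outcome; against a change score the saving is 25% at ρ = 0.5 and 15% at ρ = 0.7.

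The conclusion rests on the schedule and sample lists, not on the assumed SDs or correlations. Its weight is moderate: the outcome is secondary, and section 3.2.1 itself doubts that follow-up is long enough to show clinical differences.

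**What to change.** - In section 6.1, delete CD4 from the sentence on retrospective control-arm testing and limit the equal-frequency statement to VL.
- In the Summary and section 6.1, make the between-arm CD4 comparison the month-24 CD4, with month 12 as supportive, in all randomised patients with available data, adjusted for month-6 CD4. This answers the recovery objective in section 3.2.1 and keeps the randomised comparison.
- Keep CD4 change in failing patients as descriptive only, reporting the timing of each count relative to detection and to any switch.

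No new blood draw or visit is needed, because all these counts are already in Table 4 for both arms. The costs are a protocol amendment and the possible dilution described above. One limit remains: section 5.3.1.8 excludes patients who stop or interrupt ART, or who miss two visits and are not retrieved. Their later CD4 counts would be missing under the present text, so the report should give the number with data in each arm.
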